# Breaking the cycle of reoccurring low back pain with integrated motivational interviewing and cognitive behavioural therapy to facilitate education and exercise advice: a superiority randomised controlled trial study protocol

**DOI:** 10.1186/s12889-024-19930-8

**Published:** 2024-09-05

**Keywords:** Motivational interviewing; Cognitive behavioural therapy; Low back pain

## Abstract

**Background:**

Non-specific low back pain is a common and costly global issue. Many people with low back pain live for years with ongoing symptom recurrence and disability, making it crucial to find effective prevention strategies. Motivational interviewing (MI) is an evidence-based patient-centred counselling style that helps motivate individuals to change their behaviours. In combination, MI and cognitive-behavioural therapy (MI-CBT) has the potential to yield long term improvements in pain and disability and reduce incidence of recurrence.

**Method:**

This is a two-arm superiority randomised controlled trial comparing MI-CBT and Education (*n* = 83) with Education only (*n* = 83). Participants that have recovered from a recent episode of non-specific low back pain (7th consecutive day with pain ≤ 2 on a 0–10 numeric pain rating scale) will be eligible for inclusion into the study. Both groups will receive five 30-min sessions over a 10-week period as well as the Navigating Pain booklet, homework book and a standardised exercise programme. In the intervention group, MI-CBT techniques will be used to provide individualised support, identify beliefs, and increase engagement with the resources provided. Outcomes measures include pain (current and in the last 7 days) as rated on the numeric pain rating scale. This will be used to determine recurrence (number of participants who report back pain ≥ 3 out of 10 on the numeric pain rating scale). Furthermore, self-reported (1) pain intensity; (2) pain catastrophizing; (3) fear-avoidance beliefs; (4) pain self-efficacy; (5) depression and anxiety; (6) disability will be measured. All outcomes will be measured at baseline, and again at 3-, 6-, and 12-months post allocation.

**Discussion:**

The effective delivery of self-management strategies to prevent recurrence of low back pain is an important aspect that requires urgent attention. This study will provide new information on the effectiveness of using an MI-CBT approach to facilitate self-management through education and exercise to improve low back pain outcomes. Evidence emerging from this trial has the potential to inform clinical practice and healthcare management of non-specific low back pain.

**Trial registration:**

Prospectively registered with Australian New Zealand Clinical Trials Registry: ACTRN12623000746639 (10/07/2023).

**Supplementary Information:**

The online version contains supplementary material available at 10.1186/s12889-024-19930-8.

## Introduction

Low back pain is the leading cause of disability worldwide [1–3] and is second only to the common cold as the reason for seeing a general practitioner [4]. In 2020, this condition affected 619 million people globally, with cases projected to exceed 800 million by 2050 [3]. While a significant percentage of acute back pain episodes resolve within 2 to 3 months of onset [5, 6], recurrence rates are alarmingly high, ranging from 25 to 60% at one year [7–9] leading to 20% to 30% of individuals developing chronic pain [10]. This high recurrence rate, and chronic pain trajectory, underscores the urgent need for effective prevention strategies. To address this global health challenge, clinical practice guidelines have been developed worldwide, all advocating for a biopsychosocial approach [11–13]. These guidelines emphasize initial education, advice, self-management, and the potential use of physical and psychological therapies. Patient education and exercise have shown moderate-quality evidence in alleviating acute back pain symptoms and reducing the likelihood of recurrence [11, 14]. However, achieving and maintaining adherence to these self-management strategies is often an issue [15], despite being a key component of the effectiveness of these types of treatments [16].

Given the persistently high recurrence rates, there is a compelling need to explore innovative approaches to enhance the uptake and adherence to patient education and exercise advice. The integration of Motivational Interviewing (MI) and Cognitive-Behavioural Techniques (CBT) into pain education and exercise advice emerges as a promising avenue for addressing the burden of low back pain recurrence.

Patient education typically focuses on improving self-management by providing information about the nature of pain and encouraging the continuation of normal activities [12]. Worldwide, a range of pain education booklets for patients have been developed by health professionals, researchers, and professional organisations (e.g., Navigating Pain by the New Zealand Pain Society). Recommended exercise prescription varies, encompassing different types of exercise (e.g., advice to stay active, stretching, aerobic exercise, motor control exercises, yoga, tai-chi) and modes of delivery (group, individual, self-guided, supervised) [13]. Some evidence suggests that education and exercise can reduce the recurrence of back pain by up to 45% at 12-months [17]. However, the efficacy of education and exercise for patients with acute low back pain is equivocal [8, 9]. For example, individualised pain education was no different from placebo (listening, showing interest, giving attention) for both acute and 12-month reductions in pain as well as healthcare seeking behaviour [8]. Similarly, 12-weeks of individualised exercise and education which covered anatomy, function, back pain risk factors, and activity, did not differ significantly from providing a ‘Managing Back Pain’ booklet in preventing back pain recurrence at 12-months [9]. The lack of positive outcomes in these studies could be attributed to several factors, including suboptimal exercise adherence, and not addressing individual psychosocial factors or pain beliefs. Neither study supplemented their patient interactions and delivery of education or advice with a behavioural technique such as MI, which provides for a bespoke delivery of information [18].

MI is a directive, evidence-based patient-centred counselling style that supports an individual’s motivation to change [19, 20]. MI has demonstrated effectiveness in promoting health-related behaviour change across various populations and health conditions [18, 21–26]. In people with acute and sub-acute low back pain, MI has been shown to improve functional capacity when used as an adjunct to physiotherapy [27]. Although some evidence has explored the use of MI for individuals with chronic low back pain [28–30], no study has investigated the potential of MI to augment patient education and exercise for preventing back pain recurrence. MI might play a pivotal role in preventing back pain recurrence and improving fidelity of evidence-based practices [20].

Cognitive behavioural therapy (CBT) is a psychosocial therapeutic method of behavioural change focussed on restructuring maladaptive beliefs and emotions as well as improving coping skills and behaviours [31]. It has been shown to be effective in improving pain, physical function, quality of life and pain catastrophizing beliefs [31–33], and is a recommended first line of treatment for chronic low back pain [11]. Additionally, combining MI with complementary treatments such as CBT, that is MI-CBT, has been shown to improve health-related outcomes such as physical activity and body composition [24]. However, to our knowledge, no previous studies have examined the potential of MI-CBT to facilitate established self-management strategies (education and exercise) for reducing back pain recurrence after an acute episode of low back pain.

This protocol paper outlines the design of a randomized controlled trial, which aims to assess the effectiveness of patient education and exercise advice facilitated by MI and CBT techniques (*Edu* + *MI-CBT*) compared to education and exercise (*Edu only*) in preventing low back pain recurrence among individuals who have recently recovered from an acute episode. The primary objectives are to examine the proportion of patients reporting pain ≥ 3 out of 10 at 3, 6 and 12 months [9] and the pain intensity reported at 12 months, between the two groups. Secondary objectives include examining changes in pain catastrophizing, fear-avoidance beliefs, pain self-efficacy, depression and anxiety, and disability, as well as monitoring ongoing treatment, medication usage and physical activity reporting. Positive findings from this trial will inform the scalable implementation of such strategies within the primary care system of New Zealand.

## Methods

This study is a two-arm superiority randomized controlled trial comparing *Edu* + *MI/CBT* vs *Edu only* for participants who have ceased treatment from an episode of acute low back pain. Potential participants who have completed treatment for an acute episode of low back pain New Zealand Chiropractic College clinic, will be screened for eligibility. Those who meet the inclusion criteria will be randomly assigned to either *Edu* + *MI/CBT* or *Edu only*. Allocation will be concealed until after the baseline measures are collected at the first session (Fig. 1). Both groups will receive standard self-management resources, which include the “Navigating Pain” booklet, homework book and an exercise programme, and have five 30-min sessions over a 10-week period. In the intervention group, MI-CBT techniques will be used to provide individualised support, identify beliefs, and increase engagement with the resources provided. In the Education only group, participants will be provided with the resources as per standard protocols for delivering health education, where participants are directed in terms of what to do, without providing any specific MI-CBT based support. All outcome measures will be assessed at 3-, 6- and 12 months follow up. The protocol follows the ‘Standard Protocol Items: Recommendations for Interventional Trials’ (SPIRIT) guidelines (Supplementary File 1) [34].

**Fig. 1 Fig1:**
[figure not shown]
Participant flow chart

### Participant eligibility and recruitment

Participants will be eligible to participate in the study if they are 18 years and older and have recovered (defined as ≥ 7 consecutive days with pain ≤ 2 on a 0–10 numeric pain rating scale) from a recent (i.e., pain onset within last 3-months) episode of acute non-specific low back pain (defined as pain in the area between the 12th rib and buttock crease not attributed to a specific diagnosis) and they have received treatment for this at the New Zealand College of Chiropractic Clinic.

Participants will be excluded from the study if they have any specific low back pain diagnosis (e.g., discitis, malignancy, axial spondyloarthropathy); radiating or referred pain past the buttock; previous spinal surgery; have had any back pain in the last year prior to the most recent episode that has required them to seek treatment from an allied health professional or take pain relieving medication; diagnosed with any co-morbidity that prevents participation in exercise; inadequate English language that prevents completion of outcome measure assessment or engagement in the intervention.

The study will be conducted at the community clinic of the New Zealand (NZ) Chiropractic College in Auckland, New Zealand. Participants are invited to participate in the study by Chiropractors and administrative staff at the community clinic, after completion of their low back pain treatment. Potential participants will be screened telephonically for eligibility prior to inclusion. The researchers will discuss the trial protocol and provide the participant information sheet to eligible participants (Supplementary File 2). Consent will be taken by a researcher/s trained in Good Clinical Practice (GCP). Participants will be given the opportunity to provide consent in-person, electronically, or by mail (Supplementary File 2).

### Blinding and randomisation

After consent is provided, included participants will be randomly allocated to either *Edu* + *MI-CBT* or *Edu only* using a computer-generated alphanumeric code. A researcher ([name]) not involved in the recruitment, enrolment, or data collection will generate the allocation sequence and perform the randomisation. Randomisation will use a 1:1 allocation ratio. A sealed envelope with the participant’s group assignment will be presented to the researcher at the time of the first session.

Participants will be informed that the trial is comparing two interventions, both involving provision of education and exercise, but will be blinded to method of delivery. Unblinded researchers will carry out both interventions and enter the data into coded files to ensure group membership is blinded during analysis. Researchers performing the data analysis will be blinded to the groups. There is no foreseeable requirement for unblinding participants during the study.

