### Primary outcomes

The primary outcome measures are proportion of participants reporting low back pain (current and in the last 7 days) ≥ 3 out of 10 (using the numeric pain rating scale, 0 (no pain) to 10 (worst possible pain) at 3, 6 and 12 months; and pain intensity (current and in last 7 days) reported at 12 months [35].

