
In the *Edu-only* intervention, standard essential resource materials are provided, in commonly used directive manner that will actively refrain from offering individualized support or incorporating MI-CBT elements. Specifically, research clinicians will actively listen, express interest, and provide undivided attention to participants without employing specific MI-CBT-based support or tailored pain education advice. Instead, participants will be directed to utilize the 'Navigating Pain' booklet in its standard form or receive answers directly quoted from its content, without customization or additional guidance. Furthermore, they will be advised to adhere to the exercise program. This approach distinguishes the *Edu-only* intervention by its emphasis on question–answer driven discussions and the deliberate absence of MI-CBT elements, ensuring a clear differentiation from the MI-CBT intervention group.

The two researchers undertaking data collection will undergo training on MI-CBT practises, involving the equivalent of a 2-day initial training by a Motivational Interviewing Network of Trainers (MINT) qualified trainer, and thereafter 2 sessions of individualised training. The trial will be conducted at one site, and adherence to protocol will be monitored by the larger research team.

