### Intervention fidelity

Proficiency in the delivery of MI will be assessed using the Motivational Interviewing Treatment Integrity scale 4.2.1 (MITI 4.2.1) [42], and the Behaviour Change Counselling Index (BCCI) will be used to assess researcher competence in eliciting participants thoughts and cognitions, addressing the CBT strategies of the intervention [43]. Twenty random intervention sessions (10 from each group) will be audio-recorded for analysis of intervention fidelity at various time points during the trial, including confirmation that MI-CBT techniques were not used in the *Edu-only* group. A third-party assessor trained in the use of the MITI and BCCI, and not otherwise associated with the study, will review, and score the interactions.

Participants are permitted to seek any treatment needed during the study, and details of treatment for low back pain will be collected. The allocated intervention will be discontinued if the participant chooses to withdraw for any reason, can no longer physically complete the intervention, and/or meets the exclusion criteria during the trial. In accordance with the Health and Disability Ethics Committee (HDEC) standard, any risk to the participants will be mitigated, for example, for any scores > 10 on the HADS, a registered psychologist from the research team will contact the participant to provide further guidance and support. If the research team have any further concerns, this will be raised within 24 h of notification to the Director of the community clinic, and further support can be provided through the normal clinical operational protocols [44].

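### The two unblinded researchers who deliver both interventions also collect and enter self-reported outcomes, and the article does not say how follow-up ratings are obtained

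*Protocol article*

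**What the plan says.** Two sections of the protocol article have to be read together.

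- **Delivery and data entry.** Blinding and randomisation: "Unblinded researchers will carry out both interventions and enter the data into coded files". The researchers concerned are called unblinded, and they handle both arms.
- **Data collection.** Intervention: "The two researchers undertaking data collection will undergo training on MI-CBT practises". This supplies the number of researchers and gives collection to the people trained to deliver MI-CBT.

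The planned protections are also in the text. Analysts are masked: "Researchers performing the data analysis will be blinded to the groups". Participants are told that two education-and-exercise interventions are being compared, "but will be blinded to method of delivery". Both arms have five 30-minute sessions over 10 weeks and receive the same booklet, homework book and exercise programme.

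Under Primary outcomes, the first is the "proportion of participants reporting low back pain (current and in the last 7 days) ≥ 3 out of 10" at 3, 6 and 12 months, and the second is "pain intensity (current and in last 7 days) reported at 12 months". Both come from a 0–10 numeric rating given by the participant. The abstract describes the wider outcome set in a sentence that opens "Furthermore, self-reported (1) pain intensity".

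The one independent person is described under Intervention fidelity: "A third-party assessor trained in the use of the MITI and BCCI, and not otherwise associated with the study". That person scores recorded sessions and has no stated part in collecting outcomes.

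**The concern.** When the outcome is a participant's own rating, bias can enter at two points before any analyst sees the data. The participant may shade the rating when giving it to, or through, someone with whom they have worked. The person taking or entering it may prompt, interpret or record it differently when they know the arm. Here both handling steps fall to people who know the allocation.

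The relationship with the researcher also differs by design. The MI-CBT arm builds rapport and uses affirmation, collaborative goal setting and a personal action plan. The control arm receives attentive listening without individualised support. A tendency to report or record slightly less pain in the MI-CBT arm would look like a treatment effect, and a tendency the other way would hide one.

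The binary primary outcome is sensitive to small movements. Entry requires ratings of 2 or less and recurrence is 3 or more. On whole-number ratings these are adjacent, so one point can change a participant's recurrence status.

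**Working it through.** **Who does what, step by step**

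| Step | Who | Knows the arm? |
|---|---|---|
| Baseline measures | Collected at the first session | No: allocation is concealed until afterwards (Methods) |
| Delivery, both arms | Unblinded researchers | Yes |
| Data collection | The two researchers trained in MI-CBT | Yes, at follow-up |
| Data entry | Unblinded researchers | Yes |
| Analysis | Blinded | No |

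That the delivering and collecting researchers are the same two people is an inference from joining two sections. It is the natural one, since training data collectors in MI-CBT makes sense only if they deliver it. Baseline is protected. The exposure is at 3, 6 and 12 months, so adjusting for baseline would not remove a shift that arises later. Coding the files comes after entry and leaves the recorded scores unchanged.

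**How ratings are obtained.** No text says whether follow-up ratings are self-completed, taken by telephone or taken face to face. The schedule table is not available here.

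**Size, as an illustration only.** The concern rests on no figure in the plan. The sample-size section supplies the scale.

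- Target difference 1.0 and SD 2.0, reading 1.0 ± 2.0 in that way.
- Two-sided α = 0.05 (sidedness is assumed).
- 83 per arm less 15%: 83 × 0.85 = 70.55, so 70 analysed per arm.
- Reporting shift b between arms: assumed, since the article gives none.

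For reference, a plain two-mean calculation gives 2 × (1.960 + 0.842)² × 2.0² / 1.0² = 62.8, so 63 per arm. Then 63 / 0.85 = 74.1, so 75 per arm and 150 in total, against the stated 166. The stated method includes group-by-time interactions with a correlation that is not given. The gap therefore does not show 166 to be wrong, and nothing below depends on it.

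Standard error of the difference: SE = 2.0 × √(2/70) = 0.338.

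With no true effect and a shift b, the rejection probability is P = 1 − Φ(1.96 − b/SE) + Φ(−1.96 − b/SE).

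- b = 0: 5.0%.
- b = 0.25: b/SE = 0.74, P = 11.5%.
- b = 0.5 (half the target difference): b/SE = 1.48, P = 31.6%.

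Rounding up to 71 per arm gives 11.6% and 31.9%, and smaller shifts of 0.1 and 0.2 give 6.0% and 9.2%. The plan carries last values forward, so all 83 per arm might be analysed; 0.25 and 0.5 then give 12.7% and 36.4%. These figures concern pain intensity only. The recurrence proportion was not modelled.

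**The case against.** The case on the other side has real weight.

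- **Mode of collection.** The instruments are described as self-report or self-rating, and the exclusion for inadequate English refers to participants completing the assessments. Collecting data could mean sending out and retrieving forms. The article condenses a fuller protocol in which self-completion may already be specified. This stands: a reader might infer that participants report their pain to the person who coached them, but the article does not establish it.
- **Participant blinding.** A reader might conclude that coding the files is the only protection. It is not. Participants are blinded to the method of delivery, which matters most when they rate themselves. It reduces expectation bias, but it does not blind the person who collects and enters the data.
- **Matched contact.** Session number and length are the same, and control participants also receive attentive listening. Some wish to please the researcher is therefore likely in both arms, and only a difference between arms biases the comparison. This too lowers the risk without removing it.
- **Timing.** Sessions end by about week 10, so the 12-month rating comes roughly nine months later, when any pull from rapport may have faded. That helps for 12 months but less for the 3-month recurrence measure. It does not touch recording by someone who knows the arm.
- **Assumed shifts.** The 0.25 and 0.5 points come from no document. They show what a bias of that size would do, not that one exists.

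**Conclusion.** The point holds in a limited form. On the article's own words, the two researchers who deliver both interventions also collect and enter the data while knowing the allocation, and both primary outcomes are self-rated. No blinded or independent outcome collector is named. Participant blinding and matched contact lower the risk, and analyst blinding does not reach it. Whether the risk is more than slight depends on how follow-up ratings are obtained, which the article leaves open.

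The size of any bias cannot be estimated from the documents. With SD 2.0, 70 per arm, a two-sided 5% test and no true effect, an assumed shift of 0.25 points gives about 12% false positives and 0.5 points about 32%. A reader might go further and say that a positive result could never be told apart from reporting bias. The documents do not support that, because the shift is hypothetical and self-completion away from the researchers may already be intended. The change is worth making because it is cheap now, whereas a shift already in the recorded scores could not be reliably separated out at analysis.

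**What to change.** Amend Blinding and randomisation, and the matching sentence on data collection under Intervention, to state three things:

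1. Participants complete the 3-, 6- and 12-month questionnaires themselves, through a link or mailed form sent directly to them.
2. Online answers are written straight to the database, and any paper forms are entered by someone blind to allocation.
3. The delivering researchers take no part in collecting or entering follow-up outcomes. Reminders can be automated.

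If self-completion is already the procedure, stating it and moving data entry away from the delivering researchers is enough.

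A fixed effect for the delivering researcher should not be offered as a remedy here. Both interventions are delivered by the same researchers, so such a term adjusts for differences between them and leaves an arm-specific reporting shift in place.

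The cost is setting up the form, plus reminders or paper forms for some participants. Data collection needs no extra staff, and the sample size and interventions are unchanged. Consent may already be given electronically or by mail, so remote contact is already accepted in this trial.
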